### Plans to promote participant retention and complete follow-up {18b}

To ensure high participant retention and complete follow-up throughout the study, a comprehensive strategy will be implemented. This strategy will focus on maintaining participant engagement, minimizing dropout rates, and addressing potential challenges that may arise during the study.

Engagement and retention strategies
Regular communication: Participants will be regularly contacted via phone calls, text messages, or mobile applications to provide reminders of upcoming appointments and to maintain engagement.Flexible scheduling: Follow-up visits will be scheduled at times convenient for the participants and their families, such as weekends and holidays.Incentives: To further encourage retention, participants will receive small incentives, such as gift cards or study-related materials, upon completion of key milestones (e.g., baseline, 6-month, and 12-month visits).

2.Handling withdrawals or treatment modifications

In the event that a participant decides to withdraw or is unable to complete the study, their outcome data up to the point of withdrawal will be collected. This ensures that even if they do not complete the entire study, the data they have contributed remains valuable.Reasons for withdrawal: Participants who withdraw will be asked to provide the reason for their decision (e.g., personal, logistical, or health-related issues), which will be documented for further analysis and to inform potential improvements in future studies.Changes in treatment plan: If participants need to switch to an alternative treatment, the research team will collect relevant outcome data before the change is made, ensuring that the participant’s previous data remains part of the analysis. This will allow the study to account for the impact of treatment changes on the outcomes.

3.Follow-up and data collection

In the event of missing data or uncompleted follow-up visits, efforts will be made to contact participants to reschedule and collect the necessary data. If a participant cannot be reached for any follow-up visit, the last available data will be included in the analysis, and the participant will be considered as missing for subsequent follow-up points.

By employing these strategies, we aim to minimize participant dropout, ensure high-quality follow-up data, and maximize the retention of participants throughout the 1-year study period.

### Data management {19}

Effective data management is critical for ensuring the integrity, security, and reliability of the data collected throughout the study. A comprehensive plan will be implemented for data entry, coding, confidentiality, and storage, with quality assurance measures to ensure accurate and complete data collection.Case report form: Case report forms, which will be in paper form, will be used to record clinical data in the trial, and case report forms. As original material, the CRFs will not be changed at will. The relevant information of all patients participating in the trial will be recorded timely and truthfully.Data entry: All data collected will be entered into an electronic data capture (WMU-EDC (Wenzhou Medical University, Wenzhou, Zhejiang, China) database. To prevent errors, double data entry will be used, where two separate team members will independently enter the data, and discrepancies will be resolved through a reconciliation process.Data quality control measures

Range checks: To identify potential errors, automated range checks will be applied to the data during entry. For instance, measurements outside of predefined acceptable ranges (e.g., refraction values) will trigger a prompt for review.

Consistency checks: Periodic consistency checks will be conducted to detect any discrepancies or outliers in the dataset. These checks will compare newly entered data with historical data or other clinical parameters.

Training for data collectors: All staff involved in data collection and entry will undergo standardized training on the study protocols, measurement techniques, and data entry processes to minimize human error and improve consistency.

Data security: Data will be stored on secure cloud servers with encrypted access. Hard copies of any records will be kept in locked file cabinets, accessible only to authorized personnel. An audit trail will be maintained for all data-related actions, including data entry, modifications, and access, ensuring full traceability and accountability.

Data access and monitoring: Only authorized research staff will have access to the data, and data access permissions will be strictly controlled and documented. Regular internal audits will be conducted to ensure that data collection and management processes are being followed correctly. Data integrity will be routinely monitored, and any potential issues will be addressed promptly.

By implementing these measures, we aim to ensure data accuracy, security, and confidentiality while maintaining the highest standards of data quality throughout the study.

### Confidentiality {27}

To ensure the confidentiality of participants’ personal information throughout the study, a series of measures will be implemented to protect privacy during the pre-study phase, throughout the study, and after completion. These measures will govern the collection, sharing, and storage of personal data for both potential and enrolled participants.

Participant informed consentAll participants will sign an informed consent form before entering the study, which will clearly explain how their personal information will be collected, used, stored, and shared. Participants will have the right to withdraw consent at any time and request the destruction of their personal data. The research team will ensure that participants fully understand how their personal data will be protected, and they will be given sufficient time and opportunity to ask questions or express concerns.Data collection and storageDuring the study, all personal information related to participants will be stored using coding systems to ensure that identifying information is separate from study data. Each participant will be assigned a unique identification number, and only this number will be used to identify them.Personal identifying information (e.g., name, phone number, address) will be kept in separate files from the study data and will be accessible only to authorized personnel.Participant personal information will be stored in encrypted storage systems (e.g., cloud storage) with regular security updates and checks to maintain data protection.Data sharing and accessOnly authorized researchers and relevant personnel will have access to participants’ personal information, and this access will be granted strictly for research purposes. All access to data will be controlled through a permission-based system, ensuring that only necessary personnel can view sensitive information.Personal information will not be shared unless legally required or for specific research needs. When reporting results to external entities, all published data will be anonymized to prevent the disclosure of any personal identifiers.Post-study data managementAfter the study concludes, all personal information related to participants will continue to be handled according to confidentiality agreements and will only be used for purposes directly related to the study (e.g., data analysis, final reporting).Original data will be retained for a specified period and then securely destroyed to ensure that no personal information is accessible or disclosed after the study’s conclusion.If the data needs to be used for subsequent research or publications after the study has ended, participants will be re-consented, and appropriate confidentiality measures will be applied.Through these measures, we will ensure the protection of participants’ privacy and comply with all relevant legal and ethical standards to safeguard the confidentiality of data and participants’ rights.

### Plans for collection, laboratory evaluation and storage of biological specimens for genetic or molecular analysis in this trial/future use {33}

N/A: As indicated in the outcome measures (item 12), our study does not involve the collection of biological samples.

## Statistical methods

### Statistical methods for primary and secondary outcomes {20a}

Analysis of primary outcomeIn this participant-based study, the primary outcome is the proportion of myopia onset. This outcome is measured as a binary (nominal) variable. Participants are classified as either having experienced the onset of myopia (Yes) or not (No), based on whether their cycloplegic spherical equivalent refractive error reaches or exceeds − 0.50 D in either eye at the 1-year follow-up. This is a single endpoint measure, assessed once at the end of the 1-year follow-up period. It provides a proportion of participants who experience the onset of myopia. To test the effectiveness of DIST on the primary outcomes, logistic regression including trend analysis will be used, which can both examine the overall relationship and detect potential trends related to different treatments. In addition, covariates such as baseline spherical equivalent refractive error, age, gender, and study group (Intervention vs. Control) will be included to ensure a parsimonious logistic regression model while controlling for factors known to influence myopia onset and progression.The primary analysis will be conducted on the ITT population, which is defined as all randomized participants with at least one post-baseline measurement. For all analyses, the underlying model assumptions will be rigorously evaluated. For instance, when applying logistic regression to assess the binary primary outcome, we will verify the linearity of the logit for continuous covariates using methods such as the Box–Tidwell test, assess multicollinearity via variance inflation factors (VIF), and examine residuals and influence statistics (e.g., Cook’s distance) to identify any influential outliers. Missing data will be addressed using multiple imputations by chained equations under the assumption of data missing at random (MAR), with sensitivity analyses planned to assess the impact of outliers, nonadherence, and loss to follow-up.Analysis of secondary outcomesThe secondary outcomes are intended to capture aspects of the intervention effect that are not fully reflected by the primary outcome. For example, even if the primary outcome (myopia onset) does not show a statistically significant difference, significant changes in spherical equivalent or axial length may still be observed, thereby indicating a potential benefit of the intervention in slowing myopia progression.For the three secondary outcomes: (1) the proportion of fast progressors over 1 year, (2) changes in spherical equivalent progression, and (3) changes in AL (mm) at each follow-up point, the following statistical procedures will be employed:Proportion of fast progressors (binary outcome)This endpoint will be analyzed using logistic regression. The model will estimate the odds of being classified as a fast progressor over 1 year, comparing the intervention group to the control group. Covariates to be included in the model are baseline spherical equivalent refractive error (continuous), age (continuous), and gender (categorical), as these factors have been shown in prior research to influence myopia progression. The study group (intervention vs. control) will be the primary factor of interest. These covariates are selected based on their theoretical relevance and empirical support, ensuring a parsimonious model that controls for potential confounding without overfitting.Changes in spherical equivalent progression (continuous outcome)The change in spherical equivalent progression over time will be analyzed using a repeated measures mixed-effects model. This model will account for within-subject correlations across multiple follow-up points and will include fixed effects for the treatment group, time (as a categorical or continuous variable depending on the observed pattern), and the interaction between treatment and time. Baseline spherical equivalent refractive error, age, and gender will be included as covariates to adjust for initial differences and known predictors of refractive change. The rationale for these covariates is their established association with myopia progression, ensuring that the model is both explanatory and parsimonious. Model selection procedures, such as stepwise backward elimination based on the Akaike Information Criterion (AIC) or likelihood ratio tests, will be applied to refine the final model.Changes in AL (mm)Similar to the spherical equivalent endpoint, changes in axial length (measured in mm) at each follow-up will be analyzed using a repeated measures mixed-effects model or an analysis of covariance (ANCOVA) for longitudinal data. The model will include fixed effects for treatment, time, and their interaction. Covariates will include baseline axial length, baseline spherical equivalent, age, and gender. These factors are chosen because they are known to influence ocular growth and, consequently, axial elongation. As with the other endpoints, a parsimonious model will be achieved by using stepwise selection methods or likelihood ratio tests to retain only covariates that contribute significantly to explaining the variation in axial length change.The results of these analyses will be presented as adjusted odds ratios with 95% confidence intervals for the binary outcome and as least-squares means (LSMEANS) with standard errors for the continuous outcomes. In addition, p-values will be reported to assess the statistical significance of the observed differences between intervention groups.Analysis of exploratory outcomesTime-to-myopia onset analysisFor comparing the time to myopia onset (time-to-event outcome) among 3 treatment groups, we all create a number-at-risk table and use the Kaplan–Meier method to estimate survival curves, followed by the log-rank test to assess differences statistically.Myopia onset associationsA logistic regression model will be built with myopia onset as the dependent variable and near-work duration, device usage duration, and confounding factors as independent variables. The near-work duration was derived from the near-work log cards and questionnaires, with the daily averages taken for analysis. Odds ratio (OR) and its 95% confidence interval will be estimated to determine associations while controlling for confounding.Dose–response relationship analysisWe will group near work and device usage durations (e.g., by quartiles). Use the Cochrance–Armitage trend test to analyze if there’s a dose–response relationship. Curve fitting (such as polynomial regression) can also be used to further explore the non-linear relationship between them.Choroidal thickness changesFor exploring changes in choroidal thickness during different follow-up periods among three groups, repeated measures analysis of variance (ANOVA) will be used. If significant effects are found, post hoc tests (like Bonferroni or Tukey’s) will determine specific differences.

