### Sample size {14}

To ensure adequate power for detecting differences in myopia incidence between the two intervention groups and the control group, we performed a sample size calculation based on historical data and statistical assumptions. Below, we outline the key parameters and methodological considerations underlying our determination.

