##### Alternative hypothesis (H_1_)

The incidence of myopia in the experimental (intervention) groups is lower than that in the control group.

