#### Type I error rate (alpha), power level (e.g., 80% power)

Type I error rate (α): 0.025/2 = 0.0125

Power (1-β): 80%

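### The primary analysis uses an Intervention vs. Control term and a trend, and names neither of the two arm-versus-control comparisons for which the trial was sized

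*Protocol article*

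**What the plan says.** All references are to the protocol article.

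**Sizing.** Sample size {14} sets out to give adequate power for "detecting differences in myopia incidence between the two intervention groups and the control group". The test statistic there is a Pearson chi-square for two independent proportions. The alternative is directional: "The incidence of myopia in the experimental (intervention) groups is lower than that in the control group". The error rate is given as "Type I error rate (α): 0.025/2 = 0.0125". With event rates of 54% and 21%, 80% power and a superiority margin of 0.05, the article arrives at about 50 per group, and at 64 after 20% dropout.

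**Purpose of the arms.** The Abstract asks whether DIST works alone or together with defocus. Intervention description {11a} gives the DIST arm the task of isolating the device's own effect.

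**Analysis.** Under the primary outcome in Statistical methods {20a}, "logistic regression including trend analysis will be used, which can both examine the overall relationship and detect potential trends related to different treatments". The model terms follow: "covariates such as baseline spherical equivalent refractive error, age, gender, and study group (Intervention vs. Control) will be included". The paragraph names no contrast for an individual arm and does not mention 0.0125. The fast-progressor model in the same section again has a two-level study group.

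**The concern.** The sample size belongs to two separate tests, and the analysis text describes something else. A two-level term compares control with a mixture of DIST and Combined. A trend test asks whether onset falls along an ordering of the arms. Neither is a test of DIST against control or of Combined against control.

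What is at stake is the claim that the primary result can carry. Combined contains DIST plus defocus, so a benefit due to the defocus component alone is plausible. In that case the pooled term or the trend may be significant while the DIST device has no effect of its own, and the result could still be reported as showing that DIST delays onset.

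**Working it through.** **1. Reproduce the plan's sample size.** Inputs from Sample size {14}: p1 = 0.54, p2 = 0.21, alpha 0.0125, power 0.80, margin 0.05. Formula: two proportions, unpooled variance, one-sided test against the margin.

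n = [p1(1−p1) + p2(1−p2)] × (z₀.₉₈₇₅ + z₀.₈₀)² / (p1 − p2 − margin)²

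= (0.2484 + 0.1659) × (2.2414 + 0.8416)² / 0.28² = 0.4143 × 9.505 / 0.0784 = 50.2, so 51.

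Dropout: 51 / 0.80 = 63.75, so 64. Both stated figures are recovered. Among the variants tried, pooled variance with the margin gives 55 and a two-sided 0.0125 with the margin gives 59. Without the margin, n is 40 (one-sided) or 47 (two-sided). The trial was therefore sized for one device arm against control at one-sided 0.0125, done twice. The one-sidedness, and the reason for dividing by two, are inferred from this match, the directional alternative and the two stated comparisons.

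**2. What the literal analysis does if only Combined works.** Assumed rates: control 0.54, DIST 0.54, Combined 0.21; 51 per arm; one-sided 0.025; no covariates.

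*Pooled term.*
- Device rate = (0.54 + 0.21)/2 = 0.375; difference from control = 0.165.
- Overall rate = (0.54 + 0.54 + 0.21)/3 = 0.43.
- Null SE = √[0.43 × 0.57 × (1/51 + 1/102)] = 0.0849.
- SE under the alternative = √[0.2484/51 + 0.4143/(4 × 51)] = 0.0831.
- Power = Φ[(0.165 − 1.96 × 0.0849)/0.0831] = Φ(−0.02) = 49%.

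*Trend, with assumed scores 0, 1, 2 for control, DIST, Combined.*
- The statistic reduces to control minus Combined = 0.33.
- Null SE = √[2 × 0.43 × 0.57/51] = 0.0980.
- SE under the alternative = √[0.4143/51] = 0.0901.
- Power = Φ[(0.33 − 1.96 × 0.0980)/0.0901] = Φ(1.53) = 94%.

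*Direct contrast, DIST versus control at one-sided 0.0125.* The rates are equal, so a positive result is a false positive: about 1%.

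Simulation of 200,000 trials gives the same 49%, 94% and about 1%.

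**3. If both arms reach 21%,** the same formulas give about 98% for the pooled term and 95% for the trend. Significance is then likely, but the test does not say which arm produced it.

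**4. The direct contrasts at 51 per arm, one-sided 0.0125, 54% versus 21%.**
- Against the 0.05 margin: Φ(0.28/0.0901 − 2.2414) = 81%.
- Against zero difference: about 90%.
- Interval width relative to 95%: 2.2414/1.96 = 1.144, about 14% wider.

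**The case against.** **Pooling is inferred.** The article never says that the device arms are combined. The two-level label sits in a list introduced as examples of covariates and may be shorthand for a three-level factor. The sentence before it speaks of different treatments and an overall relationship, which a two-level term cannot represent. This stands, and pooling is the literal reading only. But the label recurs for fast progressors, while the same section counts three groups for time to onset and choroidal thickness. An overall three-group test would not identify an arm either.

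**A statistical analysis plan may define the contrasts.** It may. Here, though, the article does not leave the treatment term open. It states one, and that term does not match its own sample size.

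**Stronger readings that the article does not support.**
- A reader might infer that the primary comparisons will be read at 95%, which for two tests sharing a control would raise one-sided family-wise error from about 2.3% to about 4.5%. The sentence promising "adjusted odds ratios with 95% confidence intervals for the binary outcome" closes the secondary-outcome part and most naturally concerns fast progressors. The primary paragraph gives no interval level.
- A reader might infer that the trend treats the arms as ordered doses. The article gives no order or scores, so 0/1/2 is an assumption and the 94% depends on it.
- A reader might add that the trend would miss an effect confined to DIST (about 3% power with those scores). Combined includes DIST, so defocus would have to cancel the whole benefit; that case deserves little weight.
- A reader might conclude that the trial cannot attribute an effect to either arm. Randomisation, arms and sample size all support separate contrasts. The limitation lies in the tests as worded.

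**Conclusion.** The point holds as a stated mismatch between the sizing and the primary analysis. The sample size reproduces as two arm-versus-control tests at one-sided 0.0125; the primary analysis names neither and, followed as written, cannot show whether DIST alone works. If only Combined is effective, the pooled term is significant in about half of trials and the trend in about 94%, against about 1% for the contrast that asks about DIST.

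These figures assume 51 evaluable per arm, the article's rates with DIST set equal to control, scores 0/1/2, and unadjusted tests. Covariate adjustment would move them somewhat; the mismatch does not depend on them. Even if the label is shorthand, the text allows analyses that lead to different conclusions, so it should be settled before the group codes are opened.

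**What to change.** In Statistical methods {20a}:

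- Enter study group as a three-level factor with control as reference.
- Define the primary analysis as two contrasts, DIST versus control and Combined versus control, each at one-sided 0.0125 with a 97.5% two-sided confidence interval.
- Label the trend analysis supportive or exploratory. If it is kept, state the order and scores.
- Use the same three-level factor for fast progressors.
- State whether the 0.05 superiority margin from the sample size section applies to the two contrasts. Power is about 81% against the margin and about 90% against zero difference. The calculation uses the margin as a difference in proportions, so if it applies, the contrasts also need to be expressed on that scale, not only as odds ratios.

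The cost is a change of wording and intervals about 14% wider than 95% intervals. The sample size stays at 64 per arm, 192 in total.

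### The SE and AL change models are selected from the outcome data, and as worded the SE model can lose its treatment-by-time term

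*Protocol article*

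**What the plan says.** All of this is in the protocol article, Statistical methods for primary and secondary outcomes {20a}, unless stated otherwise.

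- **SE change.** A repeated-measures mixed model with fixed effects for treatment, "time (as a categorical or continuous variable depending on the observed pattern), and the interaction between treatment and time". Baseline SE, age and sex are added and justified in advance by their known association with progression. The paragraph ends with model selection: "stepwise backward elimination based on the Akaike Information Criterion (AIC) or likelihood ratio tests, will be applied to refine the final model". These are given as examples of the procedure, and no term is named as exempt.
- **AL change.** The model class is left open: "a repeated measures mixed-effects model or an analysis of covariance (ANCOVA) for longitudinal data". Treatment, time and treatment-by-time are stated as its fixed effects. Baseline AL, baseline SE, age and sex are listed separately as covariates, and the plan then uses "stepwise selection methods or likelihood ratio tests to retain only covariates that contribute significantly to explaining the variation in axial length change".
- **Fast progressors.** Logistic regression with baseline SE, age and sex fixed in advance. Its own paragraph has no selection step.
- **Reporting.** Continuous outcomes are to be given as least-squares means with standard errors. No visit is named.
- **Outcome definitions (Outcomes {12}).** SE and AL are both defined as change at every follow-up visit.
- **Timing of measurements (Data collection {18a}).** Cycloplegic refraction is done at baseline, 6 and 12 months.

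**The concern.** A randomised comparison should be estimated with a model fixed before the outcomes are seen. Here three things are left to the data: which terms stay in the SE model, how time is coded in it, and which covariates stay in the AL model. The AL model class is also undecided. AIC and likelihood ratio tests can disagree, so even the selection rule is not unique. The covariates already carry a prior justification in the same section, so selecting among them gains little.

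The sharper problem is in the SE model. Without treatment-by-time the model gives one common arm effect over all visits. That cannot answer an outcome defined at each visit. If the effect builds up over the year, the common effect is also smaller than the 12-month effect.

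The same section says that SE or AL may show a benefit even if the primary outcome does not, so these estimates and p-values may carry claims. Standard errors and p-values from the selected model take no account of the selection.

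**Working it through.** The plan gives no SD, effect size or correlation for SE or AL, so there is no figure of its own to reproduce here. The only input from the plan is the number of completers: 64 per arm with 20% dropout gives 64 × 0.8 = 51.2, taken as 51.

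**Assumed inputs.** Cycloplegic SE change at 6 and 12 months; two arms compared; a true difference of 0.15 D at 12 months that builds linearly (0.075 D at 6 months); SD of true annual change 0.40 D; measurement noise SD 0.15 D per reading, with the baseline reading shared. The noise adds 2 × 0.0225 = 0.045 to each variance and 0.0225 to the covariance.

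**Formulas.** Let V6, V12 and C be the variances and covariance of the two changes.

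- Variance of the 6-to-12-month difference: Vd = V6 + V12 − 2C.
- Weight of the 6-month visit in the common effect: w6 = (V12 − C)/Vd; the 12-month weight is 1 − w6.
- Common effect when the interaction is dropped: w6 × 0.075 + (1 − w6) × 0.15.
- Standard error of the interaction contrast: s = √(2Vd/51); its true value is 0.15 − 0.075 = 0.075.
- AIC drops one term when the likelihood ratio statistic is below 2, so P(drop) = Φ(√2 − 0.075/s) − Φ(−√2 − 0.075/s).

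**Three covariance structures.**

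| Structure | V6, V12, C | Vd | w6 | Common effect | Share of 12-month effect | s | P(drop) |
|---|---|---|---|---|---|---|---|
| Perfectly linear individual slopes | 0.085, 0.205, 0.1025 | 0.085 | 1.21 | 0.060 D | 40% | 0.058 | 54% |
| Independent increments | 0.125, 0.205, 0.1025 | 0.125 | 0.82 | 0.088 D | 59% | 0.070 | 63% |
| Compound symmetry (intercept variance 0.16, residual 0.045) | 0.205, 0.205, 0.16 | 0.09 | 0.50 | 0.113 D | 75% | 0.059 | 56% |

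Simulation with the covariance estimated from the data gives about 55%, 62% and 56% dropped, with the same common effects.

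The first row is an extreme. Its 12-month weight is 1 − 1.21 = −0.21, which is why the common effect falls below the true effect at either visit.

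**Average over all trials.** When the interaction is kept, the 12-month estimate is reported. It equals the common-effect estimate plus w6 times the estimated interaction contrast. The overall mean is therefore the common effect plus w6 × (0.075 − m). Here m = 0.075 × P(drop) − s × [φ(√2 − 0.075/s) − φ(−√2 − 0.075/s)] is the part of the contrast lost in trials that drop it.

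- Linear slopes: m = 0.018, so 0.060 + 1.21 × 0.057 ≈ 0.128 D (about 0.125 D by simulation).
- Independent increments: m = 0.022, so 0.088 + 0.82 × 0.053 ≈ 0.132 D.
- Compound symmetry: m = 0.019, so 0.113 + 0.50 × 0.056 ≈ 0.14 D.

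**Sensitivity, linear-slope structure.**

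- True 12-month difference 0.10 D: dropped in about 70%, reported 0.04 D when dropped.
- True 12-month difference 0.25 D: dropped in about 23%, reported 0.10 D when dropped; about 0.24 D over all trials.
- A 5% likelihood ratio test instead of AIC, at 0.15 D: dropped in about 73%.
- Three arms instead of two, at 0.15 D: dropped in about 57%.
- 80% of the effect present by 6 months: common effect 1.21 × 0.12 − 0.21 × 0.15 ≈ 0.115 D.
- Full effect by 6 months: 1.21 × 0.15 − 0.21 × 0.15 = 0.15 D, so no shortfall.

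**The case against.** The plan says that the SE model contains treatment, time and their interaction. The selection sentence comes straight after the covariates and the argument for parsimony, and it names no target. The AL paragraph, introduced as similar to SE, limits selection to covariates. A sensible analyst could read the SE sentence the same way and keep the interaction, which the visit-by-visit outcome definition also requires. This stands in part: losing the interaction follows from unprotected wording and is not an instruction. But elimination is applied to the final model as a whole, and two competent analysts could act differently.

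A reader might infer three stronger points that the document does not support.

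- **All secondary models are data-driven.** The fast-progressor model has fixed covariates. Only a passing remark in the AL paragraph, likening it to the other endpoints, hints otherwise.
- **AL can also lose its interaction.** Its fixed effects are stated separately, and selection there covers covariates only.
- **The reported SE effect will be far below the 12-month effect.** The 40% figure needs perfectly linear individual slopes and applies only to trials that drop the term. Other covariances give 59-75%, the average over all trials is much closer to the truth, and an early, constant effect gives no shortfall.

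It is also fair to say that under randomisation the choice of covariates does not materially bias the arm contrast, that ANCOVA could be pre-specified as validly as a mixed model, and that an analysis plan not shown may settle the models. The last point does not remove the finding, because the article prescribes selection rather than staying silent on it.

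**Conclusion.** The point holds for the SE and AL change models. The plan prescribes data-driven model selection for both. For SE the wording leaves the treatment-by-time term removable, in conflict with an outcome defined at each visit, and leaves the coding of time to the data. For AL the defects are covariates kept by significance and an undecided model class.

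For a true 12-month SE difference of 0.15 D with linear accrual, removal by AIC would be common (about 55-62% of trials). The estimate in those trials would be about 0.06-0.11 D, and about 0.125-0.14 D averaged over all trials. The SDs, noise, covariance, effect size and accrual are assumptions, since the plan gives none. The effect of selection on standard errors and p-values was not quantified.

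These are secondary outcomes. The primary analysis has no stepwise step and the sample size does not depend on them. The change should be made, but it does not threaten the trial's main result.

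**What to change.** 1. Delete the model-selection sentences from the SE and AL paragraphs.
2. Fix both models in advance: arm (three levels), categorical visit, arm-by-visit, baseline SE, age and sex, plus baseline AL in the AL model. Keep every term regardless of significance.
3. Name one AL model. The mixed model is the natural choice because it matches SE.
4. State the 12-month difference of each intervention arm from control as the main reported contrast, with the other visits also shown.

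The cost is wording and a few degrees of freedom. Sample size and the primary analysis are unaffected. Recruitment is reported as complete, so the change should be dated and in place before the outcome data are analysed.
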